## Abstract

**Background:**

Allergic rhinitis (AR) is a prevalent allergic disorder. Acupuncture has been widely utilized to alleviate allergic symptoms, and numerous studies have investigated its therapeutic effects on AR. However, due to the challenges associated with establishing appropriate placebo controls, few studies have directly compared acupuncture with sham acupuncture for AR treatment. This trial investigates the comparative effectiveness and tolerability of acupuncture vs. placebo needling for allergic rhinitis patients.

**Methods:**

This clinical trial features a stratified randomization scheme with 1:1 allocation, single-blind assessment, and a total sample size of 84 participants. After screening for inclusion, qualified subjects with perennial allergic rhinitis will be randomly allocated to treatment group(accepting acupuncture, *n* = 42) or control group (accepting sham acupuncture, *n* = 42). The intervention will last over a 4-week period. The main efficacy outcome is the change in main symptom severity assessed by the Visual Analogue Scale (VAS) after each week of treatment. Secondary outcomes include the Total Nasal Symptom Score (TNSS), Efficacy Index (%) after each treatment session, time to onset of effect, Rhinitis Quality of Life Questionnaire (RQLQ) scores after each week of treatment, and the additional use rate of anti-allergic medications.

**Conclusion:**

The findings of this study aims to evaluate the effectiveness and safety of acupuncture in treating perennial allergic rhinitis through comprehensive assessment of symptom relief, time-effect relationships, quality of life improvements, and reduction in anti-allergic medication use.

**Trial Registration:**

Chinese Clinical Trial Registry (ChiCTR2400086227).

## Introduction

1

Allergic rhinitis (AR) is a non-infectious inflammatory disease characterized by symptoms such as sneezing, rhinorrhea, nasal congestion, and nasal pruritus. The prevalence of self-reported AR ranges from approximately 2%–25% in children and 1%–40% in adults (1, 2). Based on the timing and type of allergen exposure, AR is classified into seasonal allergic rhinitis (SAR), typically triggered by outdoor allergens such as pollens or molds, and perennial allergic rhinitis (PAR), commonly caused by indoor allergens like house dust mites, molds, cockroaches, and animal dander (3, 4). Although non-life-threatening, AR significantly impairs quality of life, work/school performance, and in children, facial and vocal development (5, 6). In addition, AR patients frequently experience mental health issues, including insomnia, anxiety, depression,stress and suicidal, impair cognitive function, and contribute to fatigue, irritability, and reduced quality of life (7). AR also association with comorbidities like asthma underscores the need for effective treatments (8). Current pharmacotherapy (antihistamines, corticosteroids, leukotriene antagonists, etc.) provides rapid but transient symptom relief, often with side effects (9–11). Symptoms typically recur after discontinuation. While immunotherapy can modify disease progression, its months-to-years duration challenges patient compliance. Most patients use medications only intermittently for severe symptoms, highlighting the urgent need for safer, more sustainable therapies to improve long-term outcomes.Acupuncture,as an important therapy in traditional Chinese medicine, has been used for centuries to treat nasal disorders. In 2015, the American Academy of Otolaryngology-Head and Neck Surgery recommended acupuncture as an alternative treatment for AR (12). Our previous study (13) demonstrated that a 10-day course of acupuncture significantly reduced the severity of major nasal and ocular symptoms (*P* < 0.05). Building on these findings, we designed a single-blinded, randomized, controlled trial with an extended treatment duration to assess the effectiveness and safety of acupuncture in managing AR.

## Methods and analysis

2

### Study design and setting

2.1

This is a stratified, randomized, single-blinded, controlled trial. The study flowchart is presented in Figure 1, and the schedule of enrolment, interventions, and assessments is presented in Table 1. The study sets in acupuncture department of Yueyang Hospital of Integrated Traditional Chinese and Western Medicine, Shanghai University of Traditional Chinese Medicine, China.

**Figure 1 F1:**
[figure not shown]
Flow chart.

**Table 1 T1:** Schedule of enrolment, interventions, and assessment.

Study periosd	Erolment (0 week)	Intervention period (1–4 weeks)		Follow-up period
	Before treatment	After everytime treatment	After weekly treatment	4 weeks after the end of treatment
Eligibility screening	×			
Sign informed consent	×			
Baseline information collection	×			
Randomization	×			
Intervention				
Acupuncture		×		
Sham acupuncture		×		
Outcomes				
Symptoms VAS	×		×	×
TNSS	×	×		
Efficacy index		×		
Onset time of effect		×		
RQLQ	×		×	
Extra dosing rate of loratadine		×		×
Safety evaluation		×		

### Participant and consumer involvement

2.2

Inclusion criteria includes a diagnosis of perennial allergic rhinitis (14), between the age of 18 and 60. All participants will sign consent documents before participation. Exclusion criteria includes: Severe comorbidities (e.g.,uncontrolled hypertension, diabetes, malignancies, organ dysfunction).Nasal abnormalities, sinusitis, asthma, or prior nasal surgery. Recent use of corticosteroids/Antihistamines (1 month) or immunotherapy (1 year). Prior acupuncture experience or pregnancy/lactation. Withdrawal Criteria includes using rescue medicine 3 times/week,rescue medicine-related Adverse Event ≥Grade 2 (CTCAE v5.0); experiencing severe complications or other serious illnesses and is unable to continue cooperation. Data were analyzed by intention-to-treat (ITT).

All participants provided informed consent and could withdraw anytime. Data were used solely for research purposes.

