### Rescue medication

2.6

In case participants experience any of the following conditions:VAS score ≥7 for any of the primary nasal symptoms for >2 hours;≥10 sneezing episodes within a 24-hour period;Complete nasal obstruction affecting sleep;Symptoms subjectively evaluated by the patient as severely affecting daily activities or work and becoming intolerable.Supplemental loratadine (Xuesu Shanghai Haini Pharmaceutical Co., LTD, Shanghai, China) will be administered 10 mg every day. All investigators and participants must systematically document: (1) All instances of rescue medication including timing, dosage, and reason for use (2) Adverse reactions to rescue medication including symptom description, severity, duration, assessment of relatedness to the rescue medication, and management measures.

These measures ensure patient safety while maintaining treatment efficacy assessment integrity. Collected data will inform comprehensive therapeutic outcome analyses. Participants will be instructed to refrain from using rescue medication for 24 hours prior to Primary outcomes assessment; If a participant has used rescue medication within 24 hours before a scheduled assessment, the assessment will be postponed until at least 24 hours after the last dose. And rescue medication use will be incorporated as a covariate for both primary and secondary outcomes. This approach adjusts its potential confounding effects on symptom scores. To ensure robustness, we will conduct sensitivity analyses. Besides, we will also do exploratory subgroup analysis stratified by whever they use rescue medication or not. All results will be interpreted with this limitation explicitly stated in the Discussion.

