#### Analytical methods

2.8.4

Statistical analyses will be conducted utilizing the SAS software package, with statistical significance defined as *P* < 0.05. For continuous data following normal distribution, results will be reported as mean ± SD; non-normally distributed data will be presented as median (IQR). Continuous variables will be assessed by the *t*-test or Mann–Whitney *U*-test. Categorical data will be summarized as frequencies (percentages) and evaluated through *χ*^2^ tests or Fisher's exact tests. Additionally, time-by-treatment interactions will be analyzed employing generalized estimating equations or mixed-effects models. All statistical tests will use a 95% confidence level, considering results significant when *P* values are below 0.05.Rescue medication use will be incorporated as a covariate. To ensure robustness, we will conduct sensitivity analyses. Besides, we wil also do exploratory subgroup analysis stratified by whever they use rescue medication or not.

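### Withdrawal at three rescue uses a week does not fit the daily rescue wording, and it puts the worst outcomes at risk of loss beside an ITT claim

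*Protocol article*

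**What the plan says.** Section 2.2 (Participant and consumer involvement) lists rescue use among the reasons for withdrawal: "Withdrawal Criteria includes using rescue medicine 3 times/week". It does not define a use as a dose or a day, and it does not say whether withdrawal ends the sessions only or data collection as well. The same paragraph states "Data were analyzed by intention-to-treat (ITT".

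Section 2.6 (Rescue medication) gives four triggers for rescue, all based on symptom severity. One uses the same scale and symptoms as the primary outcome: "VAS score ≥7 for any of the primary nasal symptoms for >2 hours". Once a trigger is met, loratadine "will be administered 10 mg every day". No duration is given.

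For the primary outcome, section 2.6 adds "Participants will be instructed to refrain from using rescue medication for 24 hours prior to Primary outcomes assessment". If a dose has been taken in that window, "the assessment will be postponed until at least 24 hours after the last dose". The delay has no upper limit.

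In the analysis, "rescue medication use will be incorporated as a covariate for both primary and secondary outcomes". Sections 2.6 and 2.8.4 also promise sensitivity analyses and an "exploratory subgroup analysis stratified by whever they use rescue medication or not".

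**The concern.** Two things are at stake.

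First, staff may be unable to apply the rules consistently. A regimen that the protocol itself prescribes can, on its plain reading, lead to withdrawal within days. Two readings of one phrase would withdraw different participants.

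Second, withdrawal depends on the outcome. Rescue follows bad symptoms and repeated rescue triggers withdrawal, so the rule selects participants with high symptom scores. If acupuncture works, more of them will be in the sham arm. Should their VAS stop being collected, the remaining sham participants would look better than the sham arm as randomised, and the treatment difference would shrink. The rescue-use rate, a secondary outcome that Table 1 schedules during treatment and at follow-up, would also lose its heaviest users.

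**Working it through.** **1. The rules side by side**

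- Literal daily dosing gives 7 uses a week. The third use falls on day 3, which meets the section 2.2 criterion.
- If the daily wording is only a once-daily maximum, one or two uses a week stay below the criterion and the two sections fit together.
- Under literal daily dosing, consecutive doses are about 24 hours apart. The dose-free condition is then met only when the next dose is due, or if a dose is skipped. The 24-hour rule is in tension with daily dosing, not with the withdrawal criterion.

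**2. The plan's own sample size**

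- Inputs from section 2.8.1: means 33.6 and 29.4, SDs 5.2 and 4.8, 90% power. Two-sided alpha is taken as 0.05, as in section 2.8.4.
- Difference = 33.6 − 29.4 = 4.2. SD = √((5.2² + 4.8²)/2) = 5.00.
- A t-test needs 31 per arm (power 90.2%). With the Mann–Whitney efficiency, 31/(3/π) = 32.5, so 33. Then 33/(1 − 0.20) = 41.25, so 42 per arm and 84 in total. The plan's figures reproduce, with 33 as the number before dropout.
- Power at 4.2 is 96.7% with 42 per arm and 91.9% with 33 per arm. The second is the fair comparator, because the plan already allows for 20% dropout.

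**3. Illustration of selective loss**

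These inputs are assumptions; the article gives no withdrawal rates. Let a normal severity variable have correlation r with VAS and the same shift between arms (4.2/5.0 = 0.84 SD). Everyone above a common threshold is lost, and only completers are compared. With threshold z in an arm, completers' mean VAS improves by r × 5.0 × φ(z)/Φ(z).

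- 30% of sham withdrawn: z = 0.524, φ/Φ = 0.3477/0.70 = 0.497.
- Acupuncture: z = 0.524 + 0.84 = 1.364, so 8.6% are withdrawn; φ/Φ = 0.1573/0.914 = 0.172. Overall loss = (30 + 8.6)/2 = 19.3%.
- Completer difference = 4.2 − r × 5.0 × (0.497 − 0.172) = 4.2 − 1.62r. This gives 3.4, 3.1 and 2.7 for r = 0.5, 0.7 and 0.9.
- Simulated power of the completer t-test is 82%, 77% and 75%. Cross-check at r = 0.7: completers number 42 × 0.70 = 29.4 and 42 × 0.914 = 38.4, with SDs 4.33 and 4.66. SE = √(4.33²/29.4 + 4.66²/38.4) = 1.10 and 3.06/1.10 = 2.79, giving power of 78 to 79%.
- Losing the same numbers at random leaves about 92%.

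**4. Sensitivity to the assumed rate**

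With 20% of sham withdrawn, z = 0.842 and 1.682, so 4.6% of acupuncture withdraw. The shrinkage is r × 5.0 × (0.350 − 0.102) = 1.24r, so at r = 0.7 the difference is 3.3. By the same calculation power is about 86%, against about 94% for random loss of the same numbers.

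**5. No true effect**

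With a common threshold both arms are cut alike and the bias is about zero. If the worst were lost unequally for other reasons (5% acupuncture, 20% sham, r = 1), the bias would be about −1.2, against acupuncture.

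**The case against.** A reader might infer that the plan removes the worst responders from its analysis. The article does not say so. It states intention-to-treat directly after the withdrawal criteria and keeps rescue users in view through a covariate, sensitivity analyses and a subgroup. Follow-up after withdrawal and missing-data handling are details that a condensed article may leave to the full protocol. This stands: loss of data is a risk, not a stated rule.

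A reader might also infer that the three rules can never all be followed. That depends on reading the daily wording as continuous dosing. Recording each instance of rescue, and asking participants to refrain before assessment, both suggest episodic use. This stands too, although the phrase as printed supports either reading.

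The illustration models a completer t-test, whereas section 2.8.4 also names GEE or mixed-effects models, which could use weekly VAS values obtained before withdrawal. The withdrawal rates are assumed. A fall from 97% to 77% would overstate the cost, because random dropout is already planned for.

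Finally, postponing VAS until a participant is dose-free is a disclosed washout. Measuring on schedule, under rescue, would target a different quantity. That is a choice of estimand, not an error.

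What the objection does not remove is the stated rule itself. Withdrawal is driven by the trial's own symptoms, and neither intention-to-treat wording nor a covariate recovers VAS values that were never collected. The covariate and the subgroup also condition on a post-randomisation variable that treatment may affect.

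**Conclusion.** The point holds in limited form. Sections 2.2 and 2.6 conflict if rescue is dosed continuously and agree if the wording is a once-daily maximum, so they must be reconciled. The withdrawal criterion is outcome-dependent, and its consequence for data collection is not fixed beside an intention-to-treat statement.

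If VAS collection ended at withdrawal, a true effect would be diluted: from 4.2 to about 3.1 (2.7 to 3.4), with power of about 77% against about 92%. This assumes 30% and 9% withdrawal, a common threshold and a completer analysis; lower withdrawal rates give a smaller loss. The calculation does not show a false-positive risk, since the bias is about zero when there is no true effect and the threshold is common.

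**What to change.** - Reconcile the section 2.2 withdrawal criterion, the section 2.6 dosing wording and the 24-hour postponement. Define what counts as a use. Which clinical rule applies is for the sponsor to decide.
- State that meeting the criterion, whatever it means for study treatment, does not end data collection. VAS, TNSS, RQLQ and rescue use continue on the planned dates to week 4, with VAS and rescue use also at follow-up, as in Table 1. TNSS is tied to sessions, so it needs planned dates for participants who have stopped them.
- Analyse all randomised participants as allocated.
- Record the hours since the last rescue dose at each VAS.

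The cost is amendment wording and some further self-report questionnaires from participants who have stopped sessions. Data not collected at the time cannot be recovered later.

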### Acupoint selection

2.3

Acupoints: LI20, ST7, GB20, LI4, and GV29 on both side (Figure 2 and Table 2) were selected based on the following rationale: (1) Acupoints for allergic rhinitis recommended in textbooks “Acupuncture” (China Traditional Chinese Medicine Press, 11th Edition) (2) Effective acupoint combinations validated in our previous clinical studies. To ensure standardization and reproducibility of the protocol, we have adopted a fixed acupoint prescription without individualized modifications. While this approach may not fully align with the traditional Chinese medicine principle of individualized treatment based on syndrome differentiation, it enhances the internal validity of our research by allowing assessment of a specific acupoint combination.

**Figure 2 F2:**
[figure not shown]
The location of acupoints and sham acupoints.

**Table 2 T2:** The locations of acupoints and sham acupoints.

Acupoint	Location	Sham acupoint	location
LI20	Location in the nasolabial groove,level with the midpoint of the lateral border of the ala nasi	Sham LI20	20 mm lateral to LI20
ST7	Acupuncture Point Location On the face, anterior to the ear, in a depression between the zygomatic arch and the mandibular notch, with mouth closed.	Sham ST7	20 mm below ST7
GB20	On the nape, below the occiput, at the level of DU 16, in the depression between the upper portion of the sternocleidomastoid muscle and the trapezius	Sham GB20	20 mm lateral to GB20
LI4	On the dorsum of the hand,between the 1st and 2nd metacarpal bones, approximately in the middle of the 2nd metacarpal bone on its radial side	Sham LI4	20 cm on the radial side of LI4
GV29	On the forehead, at the midpoint between the two medial ends of the eyebrow.	Sham GV29	20 mm straight up to GV29

### Operator qualifications and standardization

2.4

All acupuncture procedures will be performed by three licensed acupuncturists with at least 5 years of clinical experience, each holding nationally recognized certification in acupuncture practice. Prior to study commencement, all operators will undergo a one-week standardization training program covering acupoint location, needle insertion depth, manipulation techniques, and safety protocols. Following training, operator consistency will be evaluated through simulated treatment sessions, requiring at least 85% concordance in key operational parameters (e.g., acupoint location accuracy, needle insertion depth, manipulation frequency) among operators.

### Interventions

2.5

Both groups will undergo 12 sessions with eye masks. Participants in the treatment group will undergo acupuncture by 0.25 × 40 mm disposable needles (Guizhou Andy Pharmaceutical Equipment Co., Ltd., Guizhou, China). Following skin sterilization, aseptic adhesive pads will be positioned GB20 on both sides, and acupuncture needles are inserted through the pads to a depth of roughly 10–15 mm, following the direction of the nasal tip. Upon needle placement, gentle and uniform twirling at a frequency of approximately 60 rotations per minute, with a rotation angle of approximately 180°-360° (STRICTA 2010 guidelines) are performed to achieve *de qi* (a characteristic sensations encompassing soreness, numbness,fullness, and a heavy feeling), which is regarded as a crucial factor for therapeutic effectiveness in acupuncture. The needles are then retained at GB20. Subsequently, aseptic adhesive pads are placed on bilateral LI20, ST7, LI4, and GV29. Acupuncture needles are inserted through the pads to depths of 10–20 mm (10 mm for LI20 and GV29; 20 mm for ST7 and LI4), following the direction of the nasal tip. After insertion, twirling manipulations are performed on all needles to achieve *de qi*. All needles are retained for 20 minutes.

Participants in the control group will receive sham acupuncture using pragmatic placebo needles (0.25 mm in diameter × 30 mm; “Andy” brand disposable sterile flat-head needles; Guizhou Andy Pharmaceutical Equipment Co., Ltd.) at non-acupoint locations (Figure 2 and Table 2). The procedures and treatment settings in the control group are identical to those in the treatment group,with the exception that neither skin penetration nor needle manipulation to elicit *de qi* is administered.

Both procedures follow Liu's research (15) and SHARE guidelines (16).

### Rescue medication

2.6

In case participants experience any of the following conditions:VAS score ≥7 for any of the primary nasal symptoms for >2 hours;≥10 sneezing episodes within a 24-hour period;Complete nasal obstruction affecting sleep;Symptoms subjectively evaluated by the patient as severely affecting daily activities or work and becoming intolerable.Supplemental loratadine (Xuesu Shanghai Haini Pharmaceutical Co., LTD, Shanghai, China) will be administered 10 mg every day. All investigators and participants must systematically document: (1) All instances of rescue medication including timing, dosage, and reason for use (2) Adverse reactions to rescue medication including symptom description, severity, duration, assessment of relatedness to the rescue medication, and management measures.

These measures ensure patient safety while maintaining treatment efficacy assessment integrity. Collected data will inform comprehensive therapeutic outcome analyses. Participants will be instructed to refrain from using rescue medication for 24 hours prior to Primary outcomes assessment; If a participant has used rescue medication within 24 hours before a scheduled assessment, the assessment will be postponed until at least 24 hours after the last dose. And rescue medication use will be incorporated as a covariate for both primary and secondary outcomes. This approach adjusts its potential confounding effects on symptom scores. To ensure robustness, we will conduct sensitivity analyses. Besides, we will also do exploratory subgroup analysis stratified by whever they use rescue medication or not. All results will be interpreted with this limitation explicitly stated in the Discussion.

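### Adjusting the primary and secondary outcomes for rescue-medication use conditions on a consequence of treatment, so the adjusted model does not estimate the intention-to-treat effect

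*Protocol article*

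**What the plan says.** Section 2.6 of the protocol article sets the rule: "And rescue medication use will be incorporated as a covariate for both primary and secondary outcomes". Its reason follows directly: "This approach adjusts its potential confounding effects on symptom scores". Section 2.8.4 repeats it without confining it to a supplementary analysis: "Rescue medication use will be incorporated as a covariate".

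Other parts of the article bear on the rule:

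- One trigger for rescue in section 2.6 is "VAS score ≥7 for any of the primary nasal symptoms for >2 hours". The other triggers are also symptom-based.
- The abstract's secondary outcomes end with "and the additional use rate of anti-allergic medications", and Table 1 schedules extra loratadine dosing under outcomes. The abstract's conclusion names "quality of life improvements, and reduction in anti-allergic medication use" among the things to be assessed.
- Section 2.2 states an intention-to-treat analysis. It also makes rescue use three times a week a withdrawal criterion.
- Section 2.6 requires 24 hours without rescue before primary assessments, promises sensitivity analyses whose content is not given, and says the limitation will be stated in the Discussion.
- Sections 2.6 and 2.8.4 both plan an "exploratory subgroup analysis stratified by whever they use rescue medication or not".
- Section 2.8.4 compares continuous variables by t-test or Mann–Whitney test, with GEE or mixed models as an addition.

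**The concern.** A confounder of a treatment comparison has to influence which treatment is received. Here a randomisation list decides that, and rescue use comes later. Rescue use depends on how bad the symptoms become, so it depends on treatment if treatment works. It marks poor response and, through the drug, may also lower the later score.

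Holding rescue use fixed compares acupuncture patients who needed rescue with sham patients who needed it, and likewise the patients who did not. These pairs are not alike. A patient who needs rescue despite effective treatment tends to have more severe underlying disease than a sham patient who needs it. The balance that randomisation gave is lost, and part of the benefit is assigned to the covariate.

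At stake is the primary estimate of a trial with 84 participants. The likely harm is an understated effect and lost power, not a false positive.

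**Working it through.** **1. Position of the covariate.** The article itself puts rescue use downstream of treatment.

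| Feature | Requirement for a confounder | The article |
|---|---|---|
| Timing | Before allocation | After randomisation (2.6) |
| Relation to allocation | Influences it | Cannot; allocation is by random sequence (2.8.2) |
| Relation to symptoms | Cause of the outcome | Triggered by symptoms, partly on the VAS itself (2.6, 2.7.1) |
| Relation to treatment | Not a result of it | A trial outcome, with a reduction to be assessed (abstract, Table 1) |

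**2. The plan's own figures.** No figure in the article concerns the rescue covariate. The effect size comes from section 2.8.1: 33.6 − 29.4 = 4.2, with pooled SD √((5.2² + 4.8²)/2) = √25.04 = 5.004. With two-sided alpha 0.05 (printed as 0.05%) and 90% power, n per group = 2 × (1.960 + 1.282)² × 25.04/4.2² = 29.8, so 30; the exact t-test needs 31. Multiplying 31 by π/3 for the Mann–Whitney test gives 32.5, so 33. Then 33/0.8 = 41.25, so 42 per group and 84 in total. The planned effect and SD are therefore a consistent starting point.

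**3. What the covariate does.** Let D be the randomised difference (sham minus acupuncture), p₀ and p₁ the proportions using rescue under sham and acupuncture, and k the within-arm VAS difference between users and non-users. In a linear model

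adjusted difference = D − k × (p₀ − p₁).

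The two estimates agree only if k = 0 or p₀ = p₁. The trial expects p₀ > p₁. The term k mixes a positive part (users are sicker) with a negative part (the drug lowers their score).

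**4. Illustrative size.** The article gives no rescue rate, drug effect or trigger–outcome correlation, so all three are assumed. Model, with 400,000 simulated patients per scenario: symptom level S = −4.2 × arm + noise of SD 5; trigger T = S + noise, with correlation ρ between T and S within arm; rescue R = 1 if T exceeds the cut-off that gives the chosen sham rate; VAS = S − g × R, where g is the residual drug effect at assessment.

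| ρ | Sham rescue p₀ | p₁ | g | D | k | Adjusted = D − k(p₀ − p₁) | Attenuation |
|---|---|---|---|---|---|---|---|
| 0.2 | 0.50 | 0.432 | 2 | 4.05 | −0.43 | 4.08 | −1% |
| 0.5 | 0.35 | 0.21 | 1 | 4.05 | 3.19 | 3.60 | 11% |
| 0.9 | 0.50 | 0.225 | 0 | 4.19 | 7.41 | 2.15 | 49% |

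The first and last rows are the extremes over ρ 0.2–0.9, sham rescue 10–50% and g 0–2. A similar model run separately gave −3% to 53%. With baseline severity also in the model, ρ = 0.7 and g = 0, an estimate of 4.19 becomes 3.57, 3.25 and 3.14 at sham rescue rates of 20%, 40% and 60%, an attenuation of 15–25%.

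In the middle row, 3.60 is neither the effect regardless of rescue (4.05) nor the effect had nobody used rescue (4.2).

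**5. No treatment effect.** Then p₀ = p₁, the extra term vanishes, and both models gave about zero.

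**6. Rough effect on power.** With 33 evaluable per group and unchanged SD, power = Φ(d/(5.004 × √(2/33)) − 1.960). This is 92.6% at d = 4.2, 81% at 3.5 and 74% at 3.2. It is only a guide, because the covariate also changes the residual SD.

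**The case against.** The strongest reply is that the plan already holds a valid comparison. The t-test and Mann–Whitney test take no covariates, the sample size rests on a comparison of two means, and the regression models are additional. This stands in part: one candidate primary estimate is free of the problem. But section 2.6 applies the covariate to the primary outcome expressly, so the article leaves open which estimate is primary.

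The safeguards in section 2.6 do not remove the problem. The 24-hour interval limits acute drug effect on the score, but rescue use still marks poor response. Unspecified sensitivity analyses and a caveat leave the covariate in place.

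A reader might infer more than the article supports:

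- *That the medication-use outcome would be adjusted for itself.* Read literally, the rule covers all secondary outcomes. But its stated purpose concerns symptom scores, and the numbered list in section 2.7.2 omits medication use. This is loose wording, not a planned analysis.
- *That the adjusted estimate answers no causal question.* If rescue use and symptoms shared no unmeasured causes, it would target a direct effect. That is doubtful here, because underlying severity drives both, but the claim is too strong.
- *That one percentage describes the bias.* Any single figure reflects assumed inputs.
- *That the user/non-user subgroup must go.* It is labelled exploratory. It needs a label as a non-randomised comparison; deletion is a preference.

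The simulations also keep every patient, whereas section 2.2 withdraws frequent rescue users. This adds to the uncertainty about size.

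**Conclusion.** The covariate rule is wrong as written and should be changed, because it reaches the primary outcome. A model with rescue use as a covariate does not estimate the intention-to-treat effect, and its stated justification as control of confounding does not hold in a randomised comparison.

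Bias towards no effect is the most plausible direction, though not certain: a weak link between trigger and outcome combined with a larger drug effect gave a very slight inflation. The range from about nil to about 50% attenuation rests wholly on the assumed inputs. The bias would vanish if acupuncture did not change rescue use, but the trial's own aims expect that it does.

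**What to change.** In sections 2.6 and 2.8.4:

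1. Remove rescue use as a covariate from the primary and secondary models.
2. Name one primary analysis: the randomised comparison of VAS regardless of rescue use, adjusted only for baseline variables (baseline VAS and the severity stratum).
3. Compare rescue use between arms as an outcome in its own right.
4. Add a sensitivity analysis that gives rescue users, or those withdrawn for rescue use, an unfavourable value.
5. Keep any rescue-adjusted model and the user/non-user subgroup only as exploratory analyses, labelled as non-randomised comparisons.

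The cost is mainly wording in two sections and the analysis plan, since rescue use is already recorded. There is one small practical cost. An analysis regardless of rescue needs VAS from participants who meet the rescue-related withdrawal criterion in section 2.2, and the article does not say that it is collected. Their scheduled VAS assessments should continue where possible, or the missing values should be handled by a stated method. No clinical rule has to change.
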